## 5. Study halting/termination and withdrawal of subjects

### 5.1 Study halting and termination rule

A temporary halting or termination for single study subjects or for the study as a whole can be decided in case of an occurrence of

- a serious adverse event (SAE)
- an unexpected grade 3 or higher systemic reaction or lab toxicity

with an at least reasonable possibility of a causal relationship to the administration of MVA-BN® (IMVAMUNE®), i.e. the relationship cannot be ruled out.

These parameters are not all-inclusive. Other adverse events could occur that would trigger a Data Safety Monitoring Board (DSMB) review. Any member of the DSMB, the Principal Investigator, BN Safety Officer, or DMID Medical Officer could request a Safety Monitoring Committee review based on any observation.

### 5.2 Reporting of events fulfilling the study halting criteria

If an event fulfilling the study halting criteria reaches the Investigator's attention, the Investigator has the liability to alert Kendle's Safety Department immediately (within 24 hours) and provide a comprehensive documentation of the event.

### 5.3 Data Safety Monitoring Board (DSMB)

The DSMB is an independent board that oversees the safety of volunteers participating in the study. The members of the DSMB are selected by BN and the DMID in accordance with the DMID guidelines. The primary responsibilities of the DSMB are to periodically review and evaluate the accumulated study data for participant safety, study conduct and progress, and make recommendations to BN, the DMID and the Principal Investigator(s) concerning the continuation, modification, or termination of the trial program. The DSMB considers study specific data as well as relevant background knowledge about the disease, test agent, and patient population under study. A separate charter describes in detail relevant operational procedures, communication pathways, roles and responsibilities of the DSMB.

In case an event occurs which fulfills the study halting criteria the DSMB will review the event in a timely manner and give a recommendation to BN, the DMID and the Principal Investigator(s) to halt, resume or terminate the study participation of the affected subject and/or the study as a whole.

### 5.4 Individual withdrawal criteria during the study

Subjects may withdraw or be removed from the study for any of the reasons cited below:

- An adverse event occurs that, in the opinion of the Investigator, makes it unsafe for the subject to continue the study. In this case, the appropriate measures will be taken.
- Subject's request to withdraw.

- Subject unwilling or unable to comply with study requirements.
- Clinical need for concomitant or ancillary therapy not permitted in the study.
- Unrelated intercurrent illness that, in the judgment of the Principal Investigator, will affect assessment of clinical status to a significant degree.

The following criteria should be checked at any visit after enrollment into the study. If any become applicable during the study, the subject may be withdrawn:

Use of any investigational or non-registered drug or vaccine other than the study vaccine(s).  
Administration of a licensed vaccine not foreseen by the study protocol during the study period.  
Start of chronic administration (defined as more than 14 days) of systemic immuno-suppressants during the study period.  
Administration of immunoglobulins and/or any blood products during the study period.

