20. Having received any vaccinations or planned vaccinations with a live vaccine within 30 days prior or after study vaccination.
21. Having received any vaccinations or planned vaccinations with a killed vaccine within 14 days prior or after study vaccination.
22. Chronic administration (defined as more than 14 days) of systemic immuno-suppressants during a period starting from six months prior to administration of the vaccine and ending at study conclusion. Subjects receiving chronic treatment (defined as more than 14 days) with topical calcineurine inhibitors (eg tacrolimus, pimecrolimus) on the body or > 25% of the facial area are excluded. A wash-out period of  $\geq 14$  days for tacrolimus and  $\geq 28$  days for pimecrolimus can be considered sufficient before enrollment into the study. Subjects receiving chronic treatment (defined as more than 14 days) with high dose topical cortisone (> 30 grams/week of an intermediate potency [class IV] topical steroid [or equivalent], the treated area must not exceed 10% of the total body surface) are excluded.

23. Post organ transplant subjects whether or not receiving chronic immunosuppressive therapy.
24. Administration or planned administration of immunoglobulins and/or any blood products during a period starting from 3 months prior to administration of the vaccine and ending at study conclusion.
25. Use of any investigational or non-registered drug or vaccine other than the study vaccine within 30 days preceding the first dose of the study vaccine, or planned administration of such a drug during the study period.
26. Study personnel.

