## 5.5 Subject withdrawal procedure

If a subject discontinues prior to completion of the study, the date and reason for the discontinuation will be obtained. The date of the last dose of study medication will also be obtained.

Once a subject receives MVA-BN® (IMVAMUNE®), he/she must be followed for safety as stated in the protocol. From the time of discontinuation, all diagnostic procedures and evaluations scheduled for the last main study visit (Visit 5) should be performed (see III. FLOW CHART).

As a general rule, subjects who discontinued the trial after having received at least one vaccination will not be replaced.

Subjects included in the study but already discontinued the trial prior to the first vaccination should be replaced.

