## 5.6 Contraindications and precautions for further study vaccinations

### Absolute contra-indications:

The following events constitute absolute contra-indications to further administration of the study vaccine; if any of these occur during the study, the subject must not receive additional doses of vaccine, but may continue other study procedures at the discretion of the Investigator. The subject must be followed until resolution of the event, as with any adverse event:

- Anaphylactic reaction following the administration of vaccine(s).
- Pregnancy.

Subjects who become pregnant during the study period (up to and including one month [minimum 28 days] after receiving the last vaccine dose) must not receive additional doses of vaccine but may continue other study procedures at the discretion of the Investigator.

Subjects should be instructed to notify the Investigator if it is determined after completion of the study that they became pregnant either during the study or within one month (minimum 28 days) after receiving the last vaccine dose. Pregnancy must be reported to BN on a Pregnancy Form within 24 hours of the Investigator's becoming aware of the event.

A pregnancy should be followed to term, any premature terminations reported, and the health status of the mother and child including date of delivery and the child's gender and weight should be reported to Bavarian Nordic after delivery.

Temporary deferral of vaccination:

The following adverse event constitutes a contra-indication to administration of the study vaccine at that point in time; if this adverse event occurs at the time scheduled for vaccination, the subject may be vaccinated at a later date or withdrawn at the discretion of the Investigator. The subject must be followed until resolution of the event, as with any adverse event:

- Acute disease at the time of vaccination. (Acute disease is defined as the presence of a moderate or severe illness with or without fever. The vaccine can be administered to persons with a minor illness such as diarrhea, mild upper respiratory infection with or without low-grade febrile illness, i.e., oral temperature  $\leq 100.4^{\circ}\text{F}$  ( $\leq 38.0^{\circ}\text{C}$ ).

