### 9.1 Sample size calculation

The sample size calculation is based on the primary immunogenicity endpoint '**MVA-specific seroconversion rate**'.

The primary hypothesis is to show that the humoral immune response of the group with diagnosed atopic dermatitis (Group 2) is not statistically inferior compared to the group with healthy subjects (Group 1) at 10-14 days after the second vaccination (Visit 4). The study should demonstrate that the Group 2 seroconversion rate is not worse than the Group 1 seroconversion rate by more than a pre-specified amount. This amount is called the non-inferiority margin ( $\Delta$ ).

Suppose  $p_1$  is the seroconversion rate in healthy subjects (group 1) and  $p_2$  is the seroconversion rate in the subjects with atopic dermatitis (group 2).

The test on non-inferiority will be applied for the following hypothesis:

$$H_0: p_2 - p_1 \leq -\Delta \quad \text{versus} \quad H_1: p_2 - p_1 > -\Delta, \text{ where}$$

$\Delta$  is the non-inferiority margin and is chosen in this trial as 5%.

From the experience in the pilot trial POX-MVA-007 in subjects with atopic dermatitis subjects, it is anticipated that the seroconversion rate in both groups reaches at least 99%.

The above hypothesis will be tested based on an exact, unconditional test for binomial differences. In addition an exact one-sided 97.5% unconditional confidence interval for the difference of proportions will be calculated. If the lower limit of this confidence interval is greater than  $\tilde{\alpha}$  5% (or equivalent the p-value of the non-inferiority test is less than 5%) then the null hypothesis will be rejected (StatXact®, Chan 1998, Agresti and Min 2001).

Assuming a significance level of 5%, a power of > 80%, expected seroconversion rates of 99% in both groups, this yields to a sample size of 124 per group (248 in total). In order to account for drop outs, a total of 130 subjects per group (260 in total) will be treated.

For the statistical consideration of the protocol extension, please refer to Appendix IV.

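### Sections 5.4 and 5.5 allow removal from the study for non-permitted therapy without keeping the Visit 4 antibody draw, which can selectively lose worsening AD subjects from the primary endpoint

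*Protocol*

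**What the plan says.** Section 5.4 lists reasons for which a subject may withdraw or be removed from the study. One is "Clinical need for concomitant or ancillary therapy not permitted in the study". A second list, to be checked at each visit, includes starting systemic immunosuppressants for more than 14 days and "Administration of a licensed vaccine not foreseen by the study protocol during the study period". Both lists are permissive.

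Section 6.6 names only two classes of limited therapy, topical calcineurin inhibitors and topical steroids.

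Section 5.5 requires continued safety follow-up of anyone vaccinated and adds: "From the time of discontinuation, all diagnostic procedures and evaluations scheduled for the last main study visit (Visit 5) should be performed". Visit 5 (section 3.2.2) includes an antibody draw, the AD interview and, for active AD, the SCORAD. Section 5.5 does not mention Visit 4.

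Section 5.6 treats anaphylaxis and pregnancy differently. Such a subject "must not receive additional doses of vaccine, but may continue other study procedures at the discretion of the Investigator".

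The primary endpoint is ELISA seroconversion at Visit 4, which is Visit 3 (dose 2) plus 10 to 14 days. Confirmatory testing is in the Per Protocol set, and the same procedures are applied descriptively to the FAS (section 9.3).

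On other vaccines, exclusion criteria 20 and 21 use windows around a study dose: 30 days for live vaccines, and for killed ones "planned vaccinations with a killed vaccine within 14 days prior or after study vaccination".

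**The concern.** Removal here means leaving the study, not only stopping vaccine. The named limits concern eczema treatment, so the subjects exposed to this route are mostly in Group 2, and the trigger is a post-vaccination event: AD bad enough to need more than is permitted. The decision is optional and made by someone who knows the group. A subject removed before Visit 4 has no Visit 4 result, so the FAS analysis misses the same people as the Per Protocol analysis and cannot act as a check on it.

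This matters because section 1.5 gives possible immune defects in AD as the reason for asking whether these patients respond adequately. If those lost respond less well, the observed Group 2 rate is too high and the comparison is tilted towards non-inferiority.

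The vaccine clause raises a smaller question. A killed vaccine some months after dose 2 lies outside the window in criterion 21, yet falls within the study period named in 5.4. In the main phase, withdrawal for that reason could cost the F-U antibody sample.

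**Working it through.** **Inputs from the protocol.** Section 9.1: "Assuming a significance level of 5%, a power of > 80%, expected seroconversion rates of 99% in both groups". The margin "is the non-inferiority margin and is chosen in this trial as 5" percentage points. "In addition an exact one-sided 97.5% unconditional confidence interval for the difference of proportions will be calculated", so I used one-sided 2.5%. (The p-value rule beside it says 5%, which is not equivalent.) Group totals are 230 healthy and 330 AD (Appendix V).

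**The plan's own figure.** An exact unconditional test with score ordering, 99% in both groups and one-sided 2.5%, gives power 73.9% at 124 per group and 81.8% at 125. The stated 124 is therefore reproduced to within one subject. The allowance for dropout is 124/0.95 = 130.5, against 130 planned. Power is not the issue: with 218 healthy and 250 to 313 AD evaluable (218 and 313 being 230 and 330 less about 5%), it stays at or above 99%.

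**Bias.** Let w be the share of AD subjects lost before Visit 4 and s the rate at which they would have seroconverted. With 99% in everyone else:

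- true AD rate = (1 − w) × 0.99 + w × s
- bias in the observed AD rate = w × (0.99 − s)

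The protocol gives neither w nor s, so both are assumptions.

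**Effect on the conclusion.** Farrington–Manning score test, 230 v 330, margin 5 points, z = 1.96, healthy rate 99%:

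| w | s | True AD rate | P(non-inferiority), kept |
|---|---|---|---|
| 5% | 60% | 0.95×0.99 + 0.05×0.60 = 97.05% | 63% |
| 10% | 60% | 0.90×0.99 + 0.10×0.60 = 95.1% | 10% |
| 5% | 90% | 0.95×0.99 + 0.05×0.90 = 98.55% | 98.6% |
| 2% | 90% | 0.98×0.99 + 0.02×0.90 = 98.82% | 99.6% |
| any | 99% | 99% | 99.9% |

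With the affected subjects dropped, the probability is about 99.9% in every row (Group 2 held at 330; reducing it by w changes this by about 0.1 point at most). The exact test with 218 v 313 agrees in direction: 5% lost at s = 70% gives 99.8% dropped and 76.4% kept.

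**When bias alone uses up the margin.** Solve w × (0.99 − s) = 0.05, so s = 0.99 − 0.05/w:

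- w = 13.3%: s = 61%
- w = 10%: s = 49%
- w = 6.7%: s = 24%
- w = 5%: s = −1%, so it cannot happen at 5% or below

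The 13.3% is the pilot's 2 of 15 active-AD subjects with atopic dermatitis recorded as an adverse reaction (Table III). The 6.7% halves it, because at least half of Group 2 is to have active AD (section 4.1). The pilot table does not say who needed non-permitted therapy, so these are illustrative values.

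**The case against.** **Removal is optional and the trigger is narrow.** Section 5.4 says may, and 6.6 permits topical steroid and facial calcineurin inhibitors within limits, so many flares trigger nothing. This stands. A reader might infer that AD subjects who worsen drop out as a rule; the text supports only that they can.

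**A retained sample may not reach the primary test.** Confirmatory testing is Per Protocol, and non-permitted therapy or a missed dose 2 could be judged a relevant deviation. This stands, so the gain lies mainly in the FAS.

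**Without dose 2 there is no true Visit 4.** This stands. A one-dose titre is a different quantity: in POX-MVA-004 at this dose the ELISA GMT was 98.52 at Day 28 and 813.77 at Day 42 (Table II). After dose 2, only 10 to 14 days are exposed, and immunosuppression lasting more than 14 days cannot be completed within them.

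**Section 5.6 is not contradicted.** A reader might see a contradiction, but 5.6 governs further vaccination and 5.4 governs leaving the study, and both are permissive. Section 5.6 is useful only as the model for a fix.

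**AD safety is not seen only in those who stayed well.** A reader might infer that it is. However, 5.5 keeps safety follow-up, the Safety Set keeps anyone with one dose and any safety data, and the brought-forward Visit 5 evaluations record AD status near the event. What moves is the timing of the SCORAD.

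**One or two missing non-responders would not ordinarily change the result.** With 2 healthy failures the score test tolerates 10 AD failures, while 330 × 0.01 = 3.3 are expected. Restoring two non-responders lowers the probability of non-inferiority only from 99.9% to 98.8%.

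**The vaccine clause can be read as consistent.** A vaccine outside the windows of criteria 20 and 21 may count as foreseen. It also cannot affect Visit 4 if given months later, and extension subjects have no F-U antibody draw to lose. It is a wording point.

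**Conclusion.** The point holds as a possible selective loss with a cheap remedy. Sections 5.4 and 5.5 permit study removal for non-permitted therapy or chronic systemic immunosuppressants and do not retain the Visit 4 draw. Because the named limits concern eczema treatment, the loss would fall mainly on Group 2, and it would favour non-inferiority if those lost respond less well.

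Its size cannot be stated from the protocol. It is negligible if few are affected or if they respond nearly as well as others. It is material only under less favourable assumptions, such as 5% lost with 60% seroconversion. The protocol anticipates at least 99% in both groups and nowhere says that a flare lowers the antibody response. The finding therefore supports an amendment to data retention; it does not show that the primary result would be wrong.

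**What to change.** In sections 5.4 and 5.5, separate stopping further study vaccination from leaving the study, following the approach of 5.6:

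- A subject who meets a concomitant-treatment or other-vaccine criterion remains in follow-up unless consent is withdrawn or the investigator judges continued participation unsafe.
- The scheduled Visit 4 draw is kept if dose 2 was given. Otherwise a draw is taken at the corresponding time and reported separately as a one-dose titre.
- The scheduled Visit 5 SCORAD (where it applies) and the F-U contact are kept.
- These subjects are flagged as deviations and stay in the FAS, so that the FAS non-inferiority analysis is a real check on the Per Protocol result.
- The number meeting each criterion is reported by group.
- The licensed-vaccine clause in 5.4 is reconciled with the windows in criteria 20 and 21.

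Which therapies are permitted, and whether dose 2 is given, stay with the clinical team. The cost is amendment wording, a few extra visits for subjects who would otherwise have left, and a slightly more heterogeneous FAS.

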## 5.5 Subject withdrawal procedure

If a subject discontinues prior to completion of the study, the date and reason for the discontinuation will be obtained. The date of the last dose of study medication will also be obtained.

Once a subject receives MVA-BN® (IMVAMUNE®), he/she must be followed for safety as stated in the protocol. From the time of discontinuation, all diagnostic procedures and evaluations scheduled for the last main study visit (Visit 5) should be performed (see III. FLOW CHART).

As a general rule, subjects who discontinued the trial after having received at least one vaccination will not be replaced.

Subjects included in the study but already discontinued the trial prior to the first vaccination should be replaced.

## 5.6 Contraindications and precautions for further study vaccinations

### Absolute contra-indications:

The following events constitute absolute contra-indications to further administration of the study vaccine; if any of these occur during the study, the subject must not receive additional doses of vaccine, but may continue other study procedures at the discretion of the Investigator. The subject must be followed until resolution of the event, as with any adverse event:

- Anaphylactic reaction following the administration of vaccine(s).
- Pregnancy.

Subjects who become pregnant during the study period (up to and including one month [minimum 28 days] after receiving the last vaccine dose) must not receive additional doses of vaccine but may continue other study procedures at the discretion of the Investigator.

Subjects should be instructed to notify the Investigator if it is determined after completion of the study that they became pregnant either during the study or within one month (minimum 28 days) after receiving the last vaccine dose. Pregnancy must be reported to BN on a Pregnancy Form within 24 hours of the Investigator's becoming aware of the event.

A pregnancy should be followed to term, any premature terminations reported, and the health status of the mother and child including date of delivery and the child's gender and weight should be reported to Bavarian Nordic after delivery.

Temporary deferral of vaccination:

The following adverse event constitutes a contra-indication to administration of the study vaccine at that point in time; if this adverse event occurs at the time scheduled for vaccination, the subject may be vaccinated at a later date or withdrawn at the discretion of the Investigator. The subject must be followed until resolution of the event, as with any adverse event:

- Acute disease at the time of vaccination. (Acute disease is defined as the presence of a moderate or severe illness with or without fever. The vaccine can be administered to persons with a minor illness such as diarrhea, mild upper respiratory infection with or without low-grade febrile illness, i.e., oral temperature  $\leq 100.4^{\circ}\text{F}$  ( $\leq 38.0^{\circ}\text{C}$ ).

## 6. Study treatment

### 6.1 Investigational product

MVA-BN® (IMVAMUNE®) is a highly attenuated live vaccinia virus. MVA-BN® (IMVAMUNE®) will be provided in liquid-frozen aliquots. One dose of 0.5 ml liquid-frozen vaccine contains  $1 \times 10^8$  TCID50 Modified Vaccinia virus Ankara. MVA-BN® (IMVAMUNE®) is provided by BN. For details see current version of Investigator's Brochure.

Bavarian Nordic decided to exchange the IMVAMUNE® vaccine lot 170505 by IMVAMUNE® lot 0040707 during the study. For details, please refer to Appendix V.

### 6.2 Packaging and labelling

MVA-BN® (IMVAMUNE®) lot 0040707 is produced at Bavarian Nordic A/S and filled and labeled at the contract manufacturer IDT Biologika GmbH.

Address:

IDT Biologika GmbH  
[name]  
[name]  
[name]  
[contact]

The packages and vials will be labeled according to the national law of the respective study site.

### 6.3 Vaccine storage, handling and dispensing

The liquid frozen MVA-BN® (IMVAMUNE®) vaccine has to be stored at  $-20^{\circ}\text{C} \pm 5^{\circ}\text{C}$  /  $-4^{\circ}\text{F} \pm 9^{\circ}\text{F}$ . Do not re-freeze a vial once it has been thawed.

For administration, the vaccine vial will be thawed at room temperature. To ensure homogeneity, upon thawing the vial will be swirled gently (not shaken!) for at least 30 seconds. After thawing, the drug product should appear as a pale milky colored suspension. The liquid vaccine should be visually inspected for any foreign particulate matter prior to administration. In case foreign particulate matter is visible, the vaccine must not be used anymore.

The injection volume of 0.5 ml per dose will be withdrawn with a syringe using an injection needle long enough to reach the bottom of the vial. After withdrawal of the vaccine, the injection needle should be changed and the vaccine administered to the subject immediately.

If the vaccine cannot be administered immediately, it is recommended to administer the product within 12 hours after thawing. During this time the thawed vaccine vial has to be stored at  $+2^{\circ}\text{C}$  to  $+8^{\circ}\text{C}$  /  $35.6^{\circ}\text{F}$  to  $46.4^{\circ}\text{F}$  in the dark.

Details on vaccine handling can be found in Bavarian Nordic's SOP, SOP/CLIN/16, entitled "Storage, Handling and Preparation of Liquid Frozen MVA-BN for Vaccination".

